### Other outcomes

The key secondary outcomes include the individual components of the primary outcome. Other outcomes include the number of attempts to achieve arterial puncture, successful CFA cannulation, venipunctures, closure device failure, and the total time to obtain femoral access.

## Study Procedures

At discharge, a blinded investigator assessed the presence of a major vascular complication or major bleeding. We also perform a comprehensive chart review and telephone follow-up within 30 days postprocedure, to assess for complications.

### Angiographic core laboratory evaluation

Blinded research personnel will analyze peripheral angiograms in an angiographic core laboratory located at the Hamilton General Hospital, Hamilton, Ontario, Canada. We will tabulate the location of the femoral bifurcation, the presence of femoral artery calcification, the site of femoral artery cannulation, active bleeding, and femoral artery dissection.

## Statistical Considerations

The initial sample size was based on the definition used in the **R**ad**i**al **v**s Femor**al** Access for Coronary Angiography or Intervention (RIVAL) trial in patients with acute coronary syndromes of major vascular complications, and the study used a 3% expected event rate in the control arm and a 1% expected event rate in the experimental arm. These assumptions led to a sample size of 1538 patients, in order to have 80% power with a 2-sided 5% type 1 error level.^12^

A limitation of our initial sample size calculation is that BARC 2 bleeding information was not collected in the RIVAL trial, and therefore it did not have an accurate assessment of event rates. As a result, we re-estimated our sample size based on blinded event rates after enrolling 450 patients. Our revised control event rate was estimated to be 14%. Subsequently, 600 patients were needed to have 80% power, a 2-sided 5% type 1 error level, and a 50% relative risk reduction for the primary outcome. We amended the protocol on April 12, 2021. Power calculations were performed using PASS (version 13, NCSS Statistical Software, Kaysville, UT). Recruitment took longer than expected due to the COVID-19 pandemic halting all non-COVID-19-related research during periods of 2020.

For the primary analysis, an intention-to-treat analysis will include all randomized patients.^13^ In this way, patients will be kept in the treatment group to which they were originally randomized. A secondary as-treated analysis will also be performed. A χ^2^ test or Fisher’s exact test will be performed on a per-patient basis, and statistical significance will be claimed if the *P* value is less than 0.05. Of note, core-lab analyses will be performed on a per-access basis. Odds ratios and 95% confidence intervals will also be reported to quantify treatment effects.

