**Methods:**

The **U**ltrasou**n**d Gu**i**dance for **V**ascular Acc**e**ss fo**r** Cardiac Procedure**s**: **A** Randomized Tria**l** (UNIVERSAL) is a multicentre, prospective, open-label, randomized trial with blinded outcomes assessment. Patients undergoing coronary angiography with or without intervention via a femoral approach with fluoroscopic guidance will be randomized 1:1 to US-guided femoral access, compared to no US. The primary outcome is the composite of major bleeding based on the BARC 2, 3, or 5 criteria or major vascular complications within 30 days. The trial is designed to have 80% power and a 2-sided alpha level of 5% to detect a 50% relative risk reduction for the primary outcome based on a control event rate of 14%.

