## Hypothesis

Although fluoroscopy readily identifies the location of the femoral head, US allows the operator to visualize the bifurcation of the common femoral artery into superficial and profunda femoral arteries, theoretically reducing the risk of cannulating above the inguinal ligament and below the bifurcation. Furthermore, US may permit the operator to avoid puncturing areas of heavy calcium and disease, potentially reducing complications during cannulation and with closure devices. Using US may reduce the number of punctures and reduce the risk of puncture of branch vessels or venous structures, thereby potentially reducing bleeding and vascular complications.

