### Control group

After locating the femoral head with fluoroscopy, the operator obtained access through palpation of the femoral artery prior to local anesthetic injection.

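### The planned as-treated analysis is an unadjusted, non-randomised contrast that would be biased against ultrasound if control patients switch because access is difficult

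*Protocol article*

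**What the plan says.** All references are to the protocol article.

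- **Analyses.** Statistical Considerations sets an intention-to-treat primary analysis of all randomised patients in their assigned groups, then states: "A secondary as-treated analysis will also be performed". It names a chi-square or Fisher's exact test, with odds ratios and 95% confidence intervals, and a claim of significance at P below 0.05. No covariate adjustment is mentioned, and the rule is not tied to one analysis set.
- **Control technique.** Under Control group, after fluoroscopy "the operator obtained access through palpation of the femoral artery prior to local anesthetic injection". The article does not mention switching to US, or from US to palpation, in either arm.
- **Mechanism.** Under Hypothesis: "Using US may reduce the number of punctures and reduce the risk of puncture of branch vessels or venous structures". Fewer punctures are part of the expected route to fewer events.
- **Setting.** The trial is open-label (Design), and operators had to be experienced and proficient in US-guided access (Operator Requirements). Patients without a palpable femoral pulse were excluded (Eligibility Criteria). The number of access attempts was recorded in both groups (Procedures).
- **Size.** After a blinded re-estimate of the control event rate at 14%, "600 patients were needed to have 80% power, a 2-sided 5% type 1 error level, and a 50% relative risk reduction".

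**The concern.** Treatment received is decided in part after randomisation, during the access attempt itself. An unblinded operator who is proficient with US and has trouble with palpation is able to turn to US. If that happens, the patient has already had the extra punctures that the trial expects to cause bleeding and vascular injury. As-treated grouping would then move this higher-risk patient, and any event, out of control and into US. The control group loses its hardest cases and the US group gains them. Baseline adjustment would not fully repair this, because the difficulty arises during the procedure and lies on the path to the outcome.

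What is at stake is interpretation. A diluted as-treated result printed beside a clear intention-to-treat result, tested at the same 5% level, could be read as contradicting it.

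**Working it through.** **The plan's own figures.** For 14% against 7% (a 50% reduction), two-sided 5% and 80% power, with pooled variance and no continuity correction:

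n per arm = [1.960 × √(2 × 0.105 × 0.895) + 0.842 × √(0.14 × 0.86 + 0.07 × 0.93)]² / 0.07² = 300 after rounding up, so 600 in total, as stated. The initial design ("3% expected event rate in the control arm and a 1% expected event rate in the experimental arm") gives 769 per arm, or 1538, also as stated. No stated figure is wrong.

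**Inputs for the as-treated check.** From the article: 14% control and 7% US event rates under intention-to-treat, 1:1 allocation. Assumed, because the article gives neither: the share c of control patients who cross to US, and their event rate d. Crossovers are taken to keep their control-arm risk, and no US-to-palpation crossover is modelled.

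**Formulas.**

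- As-treated US rate = (US rate + c × d) / (1 + c)
- As-treated control rate = (0.14 − c × d) / (1 − c)

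**True RR 0.50, d = 30%.**

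- c = 5%: US = (0.07 + 0.015)/1.05 = 0.0810; control = (0.14 − 0.015)/0.95 = 0.1316; RR = 0.62.
- c = 10%: US = (0.07 + 0.030)/1.10 = 0.0909; control = (0.14 − 0.030)/0.90 = 0.1222; RR = 0.74.

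Here the crossovers carry 0.30/0.1316 = 2.3 and 0.30/0.1222 = 2.5 times the risk of the remaining controls.

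**No true effect (14% in both arms).**

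- c = 5%, d = 25%: 0.1525/1.05 = 0.1452 against 0.1275/0.95 = 0.1342; odds ratio 1.10.
- c = 10%, d = 35%: 0.175/1.10 = 0.1591 against 0.105/0.90 = 0.1167; odds ratio 1.43.

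**Range, true RR 0.50.** Let m be the risk of crossovers relative to the other controls. The other controls then have rate r = 0.14/(1 − c + c × m), and d = m × r. Power uses 300 per arm before regrouping; under intention-to-treat it is 80%.

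| c | m | d | As-treated RR | Power |
|---|---|---|---|---|
| 2% | 2 | 27% | 0.54 | 71% |
| 5% | 1 | 14% | 0.52 | 76% |
| 5% | 2 | 27% | 0.60 | 58% |
| 5% | 3 | 38% | 0.67 | 40% |
| 10% | 1 | 14% | 0.55 | 71% |
| 10% | 2 | 25% | 0.68 | 37% |
| 10% | 3 | 35% | 0.82 | 13% |
| 10% | 5 | 50% | 1.09 | reversed |
| 15% | 4 | 39% | 1.15 | reversed |
| 20% | 3 | 30% | 1.08 | reversed |

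**The case against.** The strongest reply is that the premise is not documented. The article neither describes nor counts crossover, and the exclusion of patients without a palpable pulse removes some of the hardest palpation cases. The article also does not define as-treated. Classification might already be by first technique, and that detail, like any adjustment, may sit in an analysis plan that is not shown; its absence here is no fault. Crossover from US to palpation could occur too. The article labels the analysis secondary and gives it no confirmatory role. All of this stands, and it makes the point conditional and minor. It does not remove it: the analysis is a stated choice, and any comparison grouped by a decision taken during the procedure is not protected by randomisation.

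A reader might go further and infer that control patients did switch after difficult palpation, or that the as-treated result can readily reverse a true benefit. The article supports neither. No switching is reported, and at up to 10% crossover with event rates up to 35% in crossovers a true RR of 0.50 becomes at worst 0.82, still in favour of US.

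A last objection is that defining exposure by technique at first puncture returns an estimate close to intention-to-treat, and so adds little. That is correct, but it is the appropriate answer: a control patient first punctured by palpation received the control strategy.

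**Conclusion.** The point holds in conditional form and is minor. The planned as-treated comparison is non-randomised and, on what the article states, unadjusted. If control patients switch to US because access is difficult, it is biased against US. For a true RR of 0.50 and a 30% event rate in crossovers, it would show about 0.62 at 5% crossover and 0.74 at 10%. At 2% crossover with double risk the distortion is small (0.54). Reversal needs about 10% crossover with five-fold risk, 15% with four-fold or 20% with three-fold. The crossover rates and risks are assumptions throughout, and crossover out of the US arm is not modelled. The intention-to-treat primary analysis, and the sample size behind it, are unaffected.

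**What to change.** In Statistical Considerations, or in the analysis plan:

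1. Confine the P below 0.05 claim, among the two analysis sets, to intention-to-treat.
2. Report crossovers by arm and direction.
3. Replace the as-treated comparison with a complier average causal effect, using randomised arm as the instrument and technique at first puncture as the exposure. On the risk-difference scale this is the intention-to-treat difference divided by the between-arm difference in the proportion first punctured under US, with a bootstrap interval. It assumes that assignment affects outcome only through the technique used first, and that no patient would always receive the opposite of the assignment.
4. If as-treated is kept, classify by first technique where available and label the result descriptive and non-randomised.

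The cost is a little more analysis work and an interval slightly wider than intention-to-treat. For illustration, if 5% of controls were first punctured under US and all US-arm patients were, the estimate at the design rates would be −0.07/0.95 = −0.074, and its interval would widen by about 1/0.95, or 5%. If every first puncture followed assignment, the estimate equals intention-to-treat.

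Study status says that enrolment closed on April 29, 2022 while data collection and analyses continued. The analysis can therefore still be changed, but steps 3 and 4 depend on whether existing case report forms show the technique at first puncture. The article does not say.

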## Randomization

Using a centralized computer randomization service (ROME, Population Health Research Institute, Hamilton, Ontario, Canada), we randomized patients 1:1, stratified by planned closure-device use, to femoral arterial access either with US vs with no US. All patients were to have fluoroscopy of the femoral head prior to puncture, in both groups. We considered patients randomized as soon as the treatment allocation was provided to the operator. Allocation was blinded with a variable block size.

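### The primary test leaves out the one stratification factor; stratifying by planned closure-device use, with a risk ratio added, is a small free gain

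*Protocol article*

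**What the plan says.** - **Design.** The Randomization section states that "we randomized patients 1:1, stratified by planned closure-device use". No other stratification factor is named.
- **Test.** Statistical Considerations says that a χ² or Fisher's "exact test will be performed on a per-patient basis, and statistical significance will be claimed if the" P value is below 0.05. No stratified or adjusted analysis is named.
- **Effect measure.** The same section says: "Odds ratios and 95% confidence intervals will also be reported to quantify treatment effects". No risk ratio or risk difference is named.
- **Planned effect.** That section also says "Our revised control event rate was estimated to be 14" percent and that "600 patients were needed to have 80% power, a 2-sided 5% type 1 error level", for "a 50% relative risk reduction for the primary outcome".
- **The factor elsewhere.** Planned closure-device use reappears only in the Subgroup Analysis section, as one of the subgroup variables.

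**The concern.** Stratified randomization balances the arms on the factor, so the part of the outcome variance that lies between strata no longer adds to the variance of the treatment difference. An unstratified test still counts it. If the factor predicts bleeding or vascular complications, the standard error is too large, the P value a little too high and the confidence interval a little too wide. The Limitations section says that the trial is not powered for more modest effects and that funding did not allow a larger one, so efficiency that costs no patients is worth having.

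The second matter is scale. The trial was planned around a relative risk reduction, but the only named estimate is an odds ratio. At an event rate near 14% the two differ visibly. A reader who sets the reported odds ratio against the 50% target would read the benefit as somewhat larger than it was.

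**Working it through.** **1. The plan's own sample size.** Inputs from Statistical Considerations: 14% vs 7% (14% with a 50% reduction), two-sided 5%, 80% power, 1:1. With pooled variance and no continuity correction:

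n per arm = [1.96·√(2 × 0.105 × 0.895) + 0.8416·√(0.14 × 0.86 + 0.07 × 0.93)]² / 0.07²
= [0.8497 + 0.3625]² / 0.0049 = 299.9, so 300 per arm and 600 in total.

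The same formula at 3% vs 1% gives 769 per arm and 1538 in total, the article's initial figure. Both match exactly, so the trial was sized for the unstratified χ² test it names.

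**2. Type I error when the stratum is ignored.** The article gives neither the share of patients with a planned closure device nor the risk by stratum. Assumed: shares of 30, 50 and 70% in the higher-risk stratum, and a risk ratio between strata of 2 or 3. The common event rate under no effect is taken as 10.5%, the average of 14% and 7%.

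With share s and ratio r, the low-stratum risk is p₀ = 0.105 / (s·r + 1 − s) and the high-stratum risk is p₁ = r·p₀. The within-stratum variance is s·p₁(1 − p₁) + (1 − s)·p₀(1 − p₀), and the total is 0.105 × 0.895 = 0.0940. True type I error is about 2[1 − Φ(1.96 / √(within/total))].

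Example, s = 0.3 and r = 3: p₀ = 0.105/1.6 = 0.0656 and p₁ = 0.1969. Within = 0.3 × 0.1969 × 0.8031 + 0.7 × 0.0656 × 0.9344 = 0.0904. The ratio is 0.96, 1.96/√0.9615 = 1.999, and type I error is 4.6%.

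**3. Power.** Simulation with 200,000 runs per scenario, N = 600, 1:1 within strata, overall control rate 14%, risk ratio 0.50 in each stratum:

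| Share | Risk ratio between strata | Within/total variance | Type I error, unstratified | Power, unstratified χ² | Power, stratified | Gain (points) |
|---|---|---|---|---|---|---|
| 30% | 2 | 0.985 | 4.8% | 81.2% | 81.3% | 0.2 |
| 30% | 3 | 0.962 | 4.6% | 81.3% | 82.1% | 0.8 |
| 50% | 2 | 0.987 | 4.9% | 81.0% | 81.1% | 0.1 |
| 50% | 3 | 0.971 | 4.7% | 81.2% | 81.8% | 0.5 |
| 70% | 2 | 0.992 | 4.9% | 81.1% | 81.1% | 0.05 |
| 70% | 3 | 0.983 | 4.8% | 81.2% | 81.5% | 0.2 |

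With no risk difference between strata, the two tests have the same power (80.9% each at a 30% share). With the null rate set at 14% instead of 10.5%, the simulated type I error of the unstratified test is 4.5–4.9% for ratios of 2 to 3; the stratified test stays at 4.9–5.1%.

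In patients, the largest gain (81.34% to 82.12%) is worth [(1.96 + 0.920)/(1.96 + 0.890)]² = 1.02, or about 2% more patients: roughly 12 of 600. The smallest is worth close to nothing.

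**4. Scale.** At 14% vs 7%, the risk ratio is 0.07/0.14 = 0.50 and the odds ratio is (0.07/0.93)/(0.14/0.86) = 0.0753/0.1628 = 0.462. Conversely, an odds ratio of 0.50 against 14% means odds of 0.0814 and a risk of 0.0814/1.0814 = 7.5%. That is a risk ratio of 0.538, a 46% reduction.

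**The case against.** The case for leaving the plan alone has five parts.

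- **The test is valid.** An unstratified χ² after stratified randomization does not inflate type I error, and it is the test the sample size was built on. This stands in full. A reader might infer from the mismatch that the primary analysis is mis-specified, but the figures do not support that.
- **The gain rests on assumptions.** The article shows no stratum shares or stratum risks, and does not say that the factor was chosen because it is prognostic. This stands, and is why the size is given as a range that starts at zero.
- **Naming two tests is convention.** A reader might infer that the primary test is left open and that Fisher's test could be used, with 77.0% power at 300 per arm. That power figure is correct for Fisher's test, but the inference is weak. The wording usually means χ², with Fisher's test for sparse tables. At the planned rates the smallest expected cell for the primary outcome is 300 × 0.105 = 31.5. The individual components, such as arteriovenous fistula or ischemic limb, are key secondary outcomes where sparse tables are plausible.
- **The odds ratio is a supplement.** It is reported in addition to the test, it is a common choice, and a risk ratio can be worked out from the arm counts. So a reader should not take it as contradicting the design. What remains is that the planned estimate could be on the design scale at no cost.
- **The change is late.** Enrollment closed on April 29, 2022, and the Study status section describes analyses as ongoing. This stands: a change to the primary test must be documented as made before unblinding.

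A full analysis plan, not shown, may already contain a stratified analysis or a risk ratio. The article nevertheless states a specific method, and that is what is commented on here.

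**Conclusion.** The point holds as a free improvement of minor weight. The stated primary test omits the only factor used to stratify randomization. If that factor is prognostic with a 2- to 3-fold risk difference (assumed), type I error is about 4.6–4.9% instead of 5%, and between 0.05 and 0.8 points of power are given up. If the factor is not prognostic, nothing is lost, and stratifying costs nothing. The sample size of 600 is unaffected. Adding a risk ratio avoids confusing an odds ratio of 0.46 with the planned risk ratio of 0.50. None of this makes the primary analysis invalid or the stated power wrong.

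**What to change.** Document the following before unblinding:

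1. Primary test: Cochran-Mantel-Haenszel, stratified by planned closure-device use as recorded at randomization (not by actual use).
2. Effect measures: Mantel-Haenszel risk ratio and risk difference with 95% confidence intervals, reported alongside the odds ratio.
3. Sensitivity analysis: the unstratified χ² test as now stated.
4. Fisher's exact test: only for sparse secondary components.

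No new data or patients are needed, since the stratum was used to randomize. The cost is a dated amendment to the analysis text, with a statement that it was made without knowledge of results by arm. If the full analysis plan already stratifies, only the published description needs to be aligned. If unblinding has already occurred, keep the stated test as primary and report the stratified analysis and the risk ratio as supportive.

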## Design

UNIVERSAL is a multicentre, parallel randomized open-label trial with blinded outcome assessment comparing US-guided access to no US guidance in patients undergoing coronary angiography or percutaneous coronary intervention (PCI) on a background of fluoroscopic guidance in both groups. The trial is coordinated by the Population Health Research Institute at Hamilton Health Sciences, McMaster University, Hamilton, Ontario, Canada, and has been approved by local ethics boards. The trial is registered at ClinicalTrials.gov with identifier number NCT03537118. UNIVERSAL is an investigator-initiated trial, and funding was provided by the McMaster University Division of Cardiology Innovation Fund and the Hamilton Health Sciences Foundation.

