## Subgroup Analysis

We will perform multiple a priori subgroup analyses to identify potential differing treatment effects in the following groups: age ( ≥ 75 years vs < 75 years), sex (male vs female), body mass index ( ≥ 30 kg/m^2^ vs < 30 kg/m^2^), peripheral vascular disease (presence vs absence), clinical presentation (non-ST elevation acute coronary syndrome vs elective), coronary intervention (PCI vs angiography alone), type of procedure (chronic total occlusion procedure vs nonchronic total occlusion procedure), sheath size ( ≥ 7 French vs < 7 French), planned closure device (planned vs not planned), and actual closure device use (used vs not used). The underlying hypothesis is that US-guided access will be more beneficial to higher-risk groups. No statistical adjustment will be made for multiple testing.

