### Limitations

The 50% reduction in the primary outcome was derived from meta-analyses; however, the UNIVERSAL trial is not powered for more modest but clinically important differences. A larger trial powered for smaller effect sizes would have been optimal but was not possible due to limitations in funding. Finally, US only addresses the method of entry; how closure is performed is important and is another avenue for preventing bleeding complications.

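### The primary test is a valid crude two-by-two comparison that makes no use of baseline risk variables already collected; a short pre-specified adjusted model would add about 0 to 4 points of power

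*Protocol article*

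**What the plan says.** The Statistical Considerations section of the Protocol article sets an intention-to-treat primary analysis of all randomized patients. The arms are compared by a chi-squared or Fisher test ("exact test will be performed on a per-patient basis, and statistical significance will be claimed" at P below 0.05), with odds ratios and 95% confidence intervals. No covariate, stratum or centre term is named.

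The same section gives the design basis: "600 patients were needed to have 80% power, a 2-sided 5% type 1 error level", with a control rate of 14% and "a 50% relative risk reduction for the primary outcome".

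Elsewhere in the article:
- **Randomization:** allocation was 1:1, stratified by planned closure-device use.
- **Table 3:** age, sex, peripheral vascular disease, indication, warfarin and NOAC use, kidney disease and other baseline variables are tabulated for 621 patients.
- **Subgroup Analysis:** age, sex, peripheral vascular disease, clinical presentation and planned closure device are among ten subgroups. The rationale given is: "The underlying hypothesis is that US-guided access will be more beneficial to higher-risk groups".
- **Limitations:** "the UNIVERSAL trial is not powered for more modest but clinically important differences", and funding ruled out a larger trial.

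**The concern.** In a trial with a binary outcome, adjusting for baseline variables that truly predict the outcome raises the power of the treatment test. It also reduces the influence of chance imbalance on the estimate. Here the variables are already in the database and enrolment has closed at 621, so precision can now be gained only through the analysis. The plan uses several of these variables for subgroup comparisons but none of them in its one confirmatory comparison.

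Two things are at stake. One is some power, in a trial that acknowledges it is weak for effects smaller than a halving of risk. The other is robustness: with few events, an uneven split of a strong risk factor could move the odds ratio. An adjusted model chosen only after the imbalance is seen would persuade nobody.

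**Working it through.** **1. Reproduce the stated sample size.** Inputs from Statistical Considerations: p1 = 0.14, p2 = 0.14 × 0.5 = 0.07, two-sided alpha 0.05 (z = 1.960), power 80% (z = 0.842), 1:1. With pooled p = 0.105:

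n per arm = [1.960 × √(2 × 0.105 × 0.895) + 0.842 × √(0.14 × 0.86 + 0.07 × 0.93)]² / 0.07²
= [0.850 + 0.362]² / 0.0049 ≈ 300, so 600 in total.

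This equals the stated figure. The initial 1538 (3% v 1%) also reproduces, at 769 per arm. Both use the uncorrected two-proportion formula, so the crude chi-squared test is the test the trial was sized for. At 621 patients the same formula gives 81.4% power.

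**2. Expected events at 621.** 310.5 × 0.14 + 310.5 × 0.07 = 43.5 + 21.7 ≈ 65.

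**3. Power with and without adjustment.** Simulated trials with 600 patients, 14% v 7%; uncorrected chi-squared test against the likelihood-ratio test for treatment in a logistic model with six baseline covariates; 14,000 trials per row. The article does not say how well any baseline variable predicts the outcome, so the control-arm c-statistic is an assumption. The simulated covariates are normally distributed, whereas most of the real ones are binary.

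| Assumed c-statistic | Crude | Adjusted | Gain (points) |
|---|---|---|---|
| 0.60 | 81.2% | 81.4% | 0.2 |
| 0.65 | 80.9% | 82.0% | 1.0 |
| 0.70 | 81.3% | 83.1% | 1.8 |
| 0.75 | 81.3% | 84.8% | 3.5 |

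The Monte Carlo standard error of each power is √(0.81 × 0.19 / 14,000) ≈ 0.3 points; both tests were applied to the same simulated trials. With covariates of no prognostic value (6,000 trials) there is no gain: 80.8% v 80.6%. A separate simulation with 621 patients and four covariates agrees: 83.1% v 84.1% at 0.64, 82.4% v 84.2% at 0.70, and 83.1% v 86.1% at 0.75.

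**4. The gain in patients.** By the formula in step 1, raising power from 80% by 1.0, 1.8 or 3.5 points would take about 16, 29 or 58 more patients.

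**5. A smaller effect.** At a relative risk of 0.6 with 621 patients, crude power is about 60%. The gains are 1.5, 1.6, 2.7 and 6.0 points at the four c-statistics (4,000 trials each; standard error of each power √(0.6 × 0.4 / 4,000) ≈ 0.8 points).

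**6. Type I error.** In one null scenario (c-statistic 0.70, 4,000 trials) the adjusted test rejected 5.6% and the crude test 5.2%. The standard error is √(0.05 × 0.95 / 4,000) ≈ 0.3 points, so a small part of the gain may be slight anti-conservatism.

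**7. The open choice of crude test.** Exact power at 14% v 7% is 81.0% for uncorrected chi-squared and 77.0% for Fisher with 600 patients, and 82.0% and 78.7% with 621. The difference at 621 is 3.3 points.

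**The case against.** The strongest reply is that nothing here is wrong. Under randomization the crude test is valid, its type I error already allows for chance imbalance, and it matches the sample-size formula. At 621 patients it exceeds 80% power if chi-squared is used. The article is also a condensed account, and an analysis plan that is not shown may already specify an adjusted model. All of this stands. What remains is that the article does name a primary test, and a better one is available at almost no cost. If the analysis plan already adjusts, only the wording needs aligning.

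Four stronger readings are tempting, and the article does not support them.

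- **That the trial is underpowered because it does not adjust.** The stated 80% is met by the chi-squared test. The gain rests on an assumed c-statistic and is about 1 point or less up to 0.65.
- **That adjustment is the only gain in power that needs no patients.** Settling on chi-squared rather than Fisher is worth about 3 points, more than adjustment yields at c-statistics up to 0.70.
- **That centre belongs in the primary model.** The Design section says "UNIVERSAL is a multicentre, parallel randomized open-label trial with blinded outcome assessment", but the article gives neither the number of centres nor the variation between them, and centre was not a stratum. With about 65 events, many centre terms could cost power.
- **That the plan itself declares these variables prognostic.** The subgroup rationale concerns differing treatment effects. It does not say which listed variables predict the composite, and anticoagulant use is not in that list. Their prognostic value is a reasonable presumption, not a statement in the article.

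The objection about timing also has force. The Study status section says that data collection and analyses are under way. Changing the primary test after results by arm are known would do more harm than good.

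**Conclusion.** The point holds as a missed efficiency. The primary comparison is crude, valid and consistent with the 600-patient calculation, but it makes no use of pre-randomization variables already in hand. Adjustment would add about 0 to 4 points of power at the design effect, and somewhat more at a relative risk of 0.6. It would also steady the estimate against chance imbalance. The size depends on an assumed control-arm c-statistic of 0.60 to 0.75 and on a covariate list that is short and fixed in advance. No figure can be given for centre.

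**What to change.** Before treatment codes are joined to outcomes, name as the primary analysis a logistic model of the 30-day composite on treatment and six adjustment variables: planned closure-device use (the randomization stratum), age (continuous), sex, peripheral vascular disease, non-ST-elevation acute coronary syndrome v elective, and oral anticoagulant use (warfarin or NOAC).

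- State which test of treatment gives the primary P value; the simulations used the likelihood-ratio test.
- Report the standardized risk difference and risk ratio with 95% confidence intervals. The adjusted odds ratio is conditional on the covariates and is not the same quantity as the crude one.
- Define clinical presentation as one two-level variable. The indications in Table 3 add up to 653 for 621 patients, so they overlap.
- Leave out sheath size, PCI performed and actual closure-device use, which may be determined after allocation.
- Use no fixed centre terms; examine centre in a sensitivity analysis.
- Keep the crude chi-squared test as a supporting analysis.

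If codes have already been joined to outcomes, keep the crude test as primary and report the adjusted model as supporting only.

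The cost is analysis-plan wording and a few lines of code, with no new data. The primary result would no longer be a single two-by-two table, and the covariate list must be fixed before unblinding.
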